**Secondary endpoint of the demonstration of cooling performance**
• Body core (bladder recommended) temperature at start of Vent2Cool procedure and every 1 min for 60 min thereafter. Then, every 15 min for an additional hour and every 2 h until 36 h after the end of Vent2Cool procedure.
• Cooling Rate in body core temperature, calculated as follows: temperature at start of Vent2Cool procedure – 33.5 °C / duration to achieve a core temperature of 33.5 °C
• Delay between the start of the Vent2Cool procedure and body core temperature of 33.5 °C
• Actual duration of the Vent2Cool procedure (from the start of the procedure on the patient to the end of the procedure)
• Delay between ROSC and body core temperature of 33.5 °C.
• Vent2Cool performance parameters based on device data recorded during the Vent2Cool procedure
**Secondary endpoints related to Vent2Cool implementation in the care pathway**
• Time of start of Vent2Cool procedure from the time of return of spontaneous circulation (ROSC).
• Time of start of Vent2Cool procedure from the patient's admission to ICU department in which it was implemented.
**Secondary criteria of survival and neurological outcome after cardiac arrest**
• Vital status after ICU discharge and/or hospital discharge (if before Day 28) and systematically at Day 28 after inclusion. In case of death, cause of death.
• modified Rankin Scale (mRS) at Day 28 after inclusion.
• Glasgow score (Glasgow coma scale) at inclusion, days 1, 2, 3 and 28 after inclusion
• SOFA score at Day 1 and 3
• Glasgow outcome score at day 28 after inclusion
• Pupillometry (presence of pupillary light reflex and Neurological pupil index (NPi)) at Day 1, 2 and 3 after cardiac arrest
• Value of the modified Cardiac Arrest Hospital Prognosis (mCAHP) Score. Scores of either < 80; [80; 105[ or > 105 predict of risk of poor outcomes of respectively at least 40%, at least 80% or at least 95%.
• Number of patients for which the mCAHP score predicted a poor outcome with a risk of at least 40% (mCAHP < 80), at least 80% (mCAHP [80; 105[) or at least 95% (mCAHP ≥ 105) vs. the total number of patients within each mRS category at Day 28.
• For patients discharged alive from hospital and / or alive at Day 28: number of days under mechanical ventilation, number of days in intensive care unit, number of days before hospital discharge, if applicable

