### Sample size and statistical analysis

The analyses will be conducted on the following patient sets: Safety population (SAF), Full Analysis Set (FAS) and Population Per Protocol (PP). The SAF includes all included and patients treated by Vent2Cool. The FAS (according to the Intent-to-Treat (ITT) principle) includes all treated patients, who had one post-baseline evaluation. The PP population includes all patients of the FAS except those with any major protocol deviation, that might significantly affect the completeness, accuracy, and/or reliability of the study data. The main endpoint analysis and secondary endpoint analyses will be based on the Full Analysis Set. A supportive analysis will be based on the Per Protocol population if more than 10% of patients are excluded from FAS.

A summary table and a flow chart will be presented for each patient population presenting the number of patients at each assessment and identifying the number of patients who withdrew over time, with the reason of premature study termination. Patients may withdraw from the study at any time, with or without reason and without prejudice to further treatment. Data that have already been collected on prematurely withdrawn patients will be retained and used for analysis, but no new data will be collected after withdrawal. Patients lost to follow-up, after hospital discharge before the end of the study, will be replaced. Data collected until the last available visit of these patients will be analyzed.

Based on an estimated success rate of around 80%, a sample of 24 analyzable patients was calculated as required to achieve sufficient precision of the success rate using Wilson's score interval, with a 95% confidence interval. Specifically, 19 of the 24 patients will have to undergo the procedure successfully, giving an expected success rate of 79.2% (95% CI [59.5%; 90.8%]).

Quantitative parameters will be described using the following summary descriptive statistics: number of patients, mean, standard deviation, median, first and third quartiles, and minimum and maximum values. Mean and standard deviation values will be reported to one decimal place greater than the data were collected. Median, first and third quartiles, minimum and maximum values will be reported with the same precision, as they were collected. Qualitative parameters will be described using frequencies and percentages.

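### The mCAHP endpoint counts risk bands against mRS-category totals, so its percentages are not on the scale of the stated band risks, and the top band's boundary differs between two bullets

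*Protocol article*

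**What the plan says.** Two adjacent bullets in Table 2 of the protocol article, under the secondary criteria of survival and neurological outcome, concern the mCAHP score.

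- The first defines bands and attaches risks: "Scores of either < 80; [80; 105[ or > 105 predict of risk of poor outcomes", which are given as at least 40%, at least 80% and at least 95% respectively. These are risks of poor outcome for a patient whose score lies in the band.
- The second defines the endpoint. Its count begins "Number of patients for which the mCAHP score predicted a poor outcome with a risk of at least 40% (mCAHP < 80" and continues through the other two bands, the last being "at least 95% (mCAHP ≥ 105". These counts are set "vs. the total number of patients within each mRS category at Day 28".

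The section on sample size and statistical analysis adds that "Qualitative parameters will be described using frequencies and percentages". It plans for 24 analyzable patients and uses a Wilson interval for the primary success rate. The article attaches no calculation to the mCAHP endpoint.

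**The concern.** The score predicts outcome from band, so the number that can be set against a stated risk is the proportion with poor outcome among patients in that band. The endpoint names the opposite total, the number of patients in each outcome category. Because categorical data are to be given as percentages, the wording leads to the share of an mRS category that belongs to each band. That share depends on how many patients happened to be enrolled in each band as well as on how they fared.

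The trial is single-arm, and the mCAHP bands are the only place in the article where a predicted risk of poor outcome appears. A reader will naturally look from the table's percentages to the 40%, 80% and 95% printed in the same bullet. On the stated base, the two sets of figures answer different questions.

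The first bullet gives the top band as above 105 and the second as 105 or above, so the two definitions do not agree.

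**Working it through.** **Reproducing the plan's own figure.** The only computed figure in the article is the Wilson interval for 19 of 24. With p = 19/24 = 0.7917, n = 24 and z = 1.96:

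- centre = (p + z²/2n)/(1 + z²/n) = (0.7917 + 0.0800)/1.1601 = 0.7514
- half-width = z·√(p(1−p)/n + z²/4n²)/(1 + z²/n) = 1.96 × √(0.00687 + 0.00167)/1.1601 = 0.1561
- interval = 59.5% to 90.8%, as stated.

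This confirms the method proposed under the fix. It says nothing about the mCAHP endpoint itself.

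**What the stated base measures.** Let n_b be the number of patients in band b and p(k|b) the probability of mRS category k in that band. The percentage on the mRS base is

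P(b|k) = n_b·p(k|b) / Σ_j n_j·p(k|j).

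The band sizes n_b stay in the expression for every category k, whether mRS is used level by level or collapsed. The stated risk is P(poor|b), which does not contain n_b.

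**Same risks, different case mix.** The documents give no band counts, so the band sizes below are assumed (total 24). The band risks are set at exactly 40%, 80% and 95%, also an assumption because the article gives them as minimum values. All poor outcomes are pooled into one category to keep the illustration short. For sizes 8/8/8, the expected numbers with poor outcome are 8 × 0.40 = 3.2, 8 × 0.80 = 6.4 and 8 × 0.95 = 7.6, total 17.2. The shares are 3.2/17.2, 6.4/17.2 and 7.6/17.2. The other rows follow the same steps.

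| Band sizes (low/mid/high) | Expected poor | Total poor | Risk within band | Share of poor outcomes by band |
|---|---|---|---|---|
| 8/8/8 | 3.2/6.4/7.6 | 17.2 | 40/80/95% | 18.6/37.2/44.2% |
| 14/6/4 | 5.6/4.8/3.8 | 14.2 | 40/80/95% | 39.4/33.8/26.8% |
| 4/6/14 | 1.6/4.8/13.3 | 19.7 | 40/80/95% | 8.1/24.4/67.5% |

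The risks are identical in all three rows, yet the percentages on the outcome base differ widely.

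**Same shares, different risks.** Suppose the 16 patients with poor outcome fall 4/8/4 across the bands, so the shares among poor outcomes are 25/50/25%. The remaining 8 patients decide the risk within each band.

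| Good outcomes by band | Poor / band total | Risk within band |
|---|---|---|
| 6/2/0 | 4/10, 8/10, 4/4 | 40/80/100% |
| 2/2/4 | 4/6, 8/10, 4/8 | 67/80/50% |
| 0/0/8 | 4/4, 8/8, 4/12 | 100/100/33% |

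The shares among poor outcomes do not by themselves identify the band risks. The counts in all outcome categories together do: adding them across categories gives the band totals used in the middle column.

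**Boundary.** Scores of 79, 80, 104, 104.9, 105.1 and 106 fall in the same band under both bullets. A score of 105 has no band under the first, because the middle band excludes 105 and the top band starts above it. Under the second it is in the top band.

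**The case against.** The wording sets one count against another. It does not prescribe a division, and it does not say that the result will be compared with the stated risks. It can fairly be read as a cross-tabulation of band by mRS. A reader might infer that the endpoint cannot be compared with the predictions at all. The document does not support that: a full cross-table with both margins yields the band totals, and the band risks follow once poor outcome is defined on the mRS. The cut-off may well stand in the full protocol or SAP, so its absence from the article is not a fault.

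Three further points stand. First, the stated risks are minimum values, so an observed risk above one of them contradicts nothing, and an exact match between outcome and prediction is not defined. Second, the illustration pools poor outcomes, whereas the text speaks of each category; the general formula shows that the dependence on case mix does not rest on pooling. Third, a reader might infer that the trial is heading for a false claim of benefit or harm. The Introduction calls the study non-comparative, the Conclusions leave clinical benefit to comparative studies, and no claim is tied to this endpoint.

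On the boundary, a reader might infer that a score of 105 is placed in two different bands. It is not: one bullet leaves it out and the other places it. The bullet that defines the counts is complete, so the first is probably a slip.

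What remains is that the only total the endpoint names is the outcome category, and percentages on that base are not on the scale of the risks quoted beside them.

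**Conclusion.** The point holds in a limited form. The endpoint as written names the wrong reference total for setting observed against predicted outcome. In the illustrations, the low-risk band's share of poor outcomes ranges from 8.1% to 39.4% with its risk fixed at 40%. Those sizes rest on assumed band counts, on risks set at their stated minimum and on pooled poor outcomes; the direction of the problem needs none of these. The boundary mismatch is certain but touches only patients scoring exactly 105.

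The consequence is confined to one descriptive secondary endpoint. The primary endpoint, the sample size and the data to be collected are not affected. It is worth correcting because the correction is simple and the trial has no control arm against which to read neurological outcome.

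**What to change.** 1. Redefine the summary as the number of patients with poor Day-28 mRS over the number of patients in each mCAHP band, using one mRS cut-off for poor outcome fixed in advance (or citing the one in the SAP if it exists).
2. Give each proportion a Wilson 95% interval, the method already chosen for the primary endpoint, and print the stated risk beside it as a floor.
3. Keep the band-by-mRS table as descriptive, with counts and both margins.
4. Use the same three bands in both bullets: below 80, from 80 to below 105, and 105 or above, as the counting bullet already does.

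The intervals will be wide. For the assumed counts 4/10, 8/10 and 4/4 they are 16.8% to 68.7%, 49.0% to 94.3% and 51.0% to 100%. The revised display puts observed and stated risks on one scale but will not support conclusions about efficacy, and the report should say so.

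The cost is a change of wording in the endpoint definition and the table shell. No new data are needed.

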**Secondary endpoints for clinical pathology**
• Urea, creatinine, ASAT, ALAT, γ-GT, blood count at inclusion, day 1 and day 3 after the Vent2Cool procedure
• Neurofilament light chain (NFL) and Neuron Specific Enolase (NSE) at inclusion, day 1 and day 3 after the Vent2Cool procedure

### Eligibility criteria

Eligible patients will be unconscious patients resuscitated after extra- or intra-hospital cardiac arrest and admitted to the Intensive Care Units (ICU). Cardiac arrest from presumed cardiac or asphyxial origin, regardless of the heart rate initially recorded, will be included. Patients must be aged between 18 and 84 years with an ideal body weight (IBW) comprised between 40 and 93 kgs. Inclusion and exclusion criteria are shown in Table 3.

**Table 3 t0015:** Summary of inclusion and exclusion criteria.

Inclusion criteria	Exclusion criteria
• Patient resuscitated after extra- or intra-hospital cardiac arrest, from presumed cardiac or asphyxial origin, regardless of the heart rate initially recorded.	• Conscious patient
• Age between 18 and 84 years old	• Patient Ideal Body Weight less than 40 kgs or more than 93 kgs
• Time between collapse and return of spontaneous circulation (ROSC) < 60 min	• Traumatic cardiac arrest, drowning, exsanguination or sepsis
• Presumption, at the time of inclusion, of a possibility of starting Vent2Cool within a period of less than 120 min after ROSC.	• Temperature at admission < 34.0 °C
• Unconscious (GCS < 8, not able to obey verbal commands after sustained ROSC)	• Need for veno-arterial extracorporeal circulation before ROSC
• Patient affiliated with a social security system (If applicable)	• One of the following signs at echocardiography at hospital admission: - Acute core pulmonale, defined by right ventricular enlargement with interventricular septal deviation, associated with a Tricuspid Annular Plane Systolic Excursion (TAPSE) < 12 mm and need for vasopressor agents - Time-velocity integral of subaortic flow < 10 m/s
• Consent of the member of patients’ family or that of the trusted person if present and able to understand; otherwise certificate of emergency inclusion in compliance with applicable regulations.	
• Vent2Cool must be connected to a standard cuffed ETT of 7.0 mm to 9.0 mm internal diameter for the procedure. For 7.0 mm ETT, the IBW setting should not exceed 75 kg. For ETTs of 7.5 to 9.0 mm, the full range of the IBW setting (i.e. 40 to 93 kg) can be applied.	
	• Wrong positioning or damage of the endotracheal tube.
	• Women under 50 years old (childbearing age) or for women of > 50 years old, a positive pregnancy test (urinary) in case of pregnancy suspicion by the investigator. Possible breastfeeding during the study.
	• Suspicion of intracranial bleeding
	• History of severe Chronic Obstructive Pulmonary Disease (COPD) with long-term home oxygen therapy
	• Acute respiratory pathology (pneumothorax, pleurisy, pneumonia, suspicion of contusion or intra-pulmonary hemorrhage following resuscitation)
	• COVID-19 positive test in case of clinical suspicion and/or epidemic context
	• Excessive mucus in the upper airways
	• Patient presenting at least one of the following criteria in the mechanical ventilation parameters at inclusion: PEEP > 8 cm H_2_O, Plateau pressure > 25 cm H_2_O, Driving pressure > 15 cm H_2_O
	• Patient with at least one of the following criteria at inclusion: PaO_2_ < 80 mmHg, PaO_2_/FiO_2_ < 150 mmHg, PaCO_2_ > 48 mmHg

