### Study intervention and target temperature management

Overall study design is illustrated by Fig. 1. After admission to the ICU and putative etiological treatment, if required, eligible patients could be included for URTH induction by Vent2Cool. Patients will be sedated and paralyzed with atracuronium and monitoring of muscle paralysis is recommended whenever possible. The maintenance of sedation and muscle paralysis after the Ven2Cool procedure will be left to the discretion of the physicians. Surface cooling device, that will be necessary to maintain hypothermia after induction by Ven2Cool, will be pre-positioned in order to avoid mobilization immediately after this procedure. However, the surface cooling system will not be active at this stage and until the end of the Vent2Cool procedure.

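### The echocardiographic exclusions are read at hospital admission, which for an in-hospital arrest comes before the arrest, so as worded they do not assess the heart after resuscitation

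*Protocol article*

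**What the plan says.** All of this is in the protocol article.

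- **Population** (Eligibility criteria, Table 3): "Patient resuscitated after extra- or intra-hospital cardiac arrest, from presumed cardiac or asphyxial origin".
- **Echocardiography** (Table 3, exclusions): "One of the following signs at echocardiography at hospital admission". Two signs follow: acute cor pulmonale with reduced TAPSE and a need for vasopressors, and a low subaortic time-velocity integral.
- **Temperature** (Table 3, exclusions): "Temperature at admission < 34.0 °C". The text does not say whether hospital or ICU admission is meant.
- **Ventilation and blood gases** (Table 3, exclusions): "Patient presenting at least one of the following criteria in the mechanical ventilation parameters at inclusion" and "Patient with at least one of the following criteria at inclusion".
- **Care pathway** (Study intervention and target temperature management): "After admission to the ICU and putative etiological treatment, if required, eligible patients could be included".
- **Implementation endpoint** (Table 2): "Time of start of Vent2Cool procedure from the patient's admission to ICU department in which it was implemented". It is listed next to the time from ROSC to procedure start.

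**The concern.** An eligibility check has to describe the patient at a time when the condition of interest can be present. Here that condition is the state of the heart after resuscitation. Hospital admission serves this purpose for an out-of-hospital arrest, because the patient arrives after ROSC. It does not for a patient who arrests during a hospital stay.

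The article describes the study as first-in-human, and the procedure fills the lungs with liquid. Major systemic hypotension during the procedure and major haemodynamic instability are among the safety endpoints in Table 1. If a site follows the text literally, a patient with new right-ventricular failure or low output could be treated, or another could be excluded on an old scan. The two centres could also apply the criterion differently. With 24 patients and no control arm, a few such cases could colour the safety description.

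**Working it through.** The main point is one of wording, so the check sets the time points side by side. The article's only design figure, the Wilson interval for 19 of 24, has no bearing on it.

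| Criterion or endpoint | Time point in the text | Out-of-hospital arrest | In-hospital arrest |
|---|---|---|---|
| Echocardiographic exclusions | Hospital admission | After ROSC | Before the arrest |
| Temperature exclusion | Admission, unspecified | After ROSC | Before the arrest if hospital admission is meant. If ICU admission is meant, after ROSC for a ward arrest moved to the ICU, and before the arrest for a patient already in the ICU |
| Ventilator exclusions | Inclusion | After ROSC | After ROSC |
| Blood-gas exclusions | Inclusion | After ROSC | After ROSC |
| ICU admission to procedure start | ICU admission | Clock starts after ROSC | After ROSC for a ward arrest; before the arrest for a patient already in the ICU |

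1. **Echocardiography.** The last column cannot be reconciled with the purpose of the criterion. The one exception is a patient who arrests in another hospital and is then transferred, for whom admission to the trial hospital follows ROSC.
2. **No back-up criterion.** No other entry in Table 3 looks at cardiac function after ROSC. The exclusion for extracorporeal circulation concerns the period before ROSC.
3. **Choice of word.** The care-pathway text and the Table 2 endpoint name the ICU when ICU admission is meant. The echocardiographic criterion names the hospital instead.
4. **Temperature.** The word is unqualified, and the article's other uses lean towards ICU admission. The criterion is therefore ambiguous, not shown to be pre-arrest. Core temperature at procedure start is recorded (Table 2), but as a performance endpoint and not as an eligibility check.
5. **Timing endpoint.** It departs from its purpose only for an arrest in a patient already in the ICU. As an illustration, assume a 3-day stay before the arrest: 3 × 24 × 60 = 4,320 min. Among 24 patients this one value would contribute 4,320 / 24 = 180 min to the mean, while inclusion presumes a start within 120 min of ROSC. The 3-day stay is an assumption; the documents mention no such patient.

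**The case against.** **Intent is evident.** The criterion speaks of acute cor pulmonale with a need for vasopressors, in a comatose patient who has been resuscitated and admitted to the ICU. That describes a post-resuscitation assessment, and investigators may well apply it so. This stands as a statement of likely intent. It also shows that the wording departs from the intent, which is a reason to correct it.

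**The article is a condensation.** Table 3 is headed as a summary, and the detailed inclusion process is in a supplementary table that is not shown. The operational timing may be there. This limits what can be said about practice: it cannot be claimed that in-hospital patients will go without an echocardiogram after ROSC. It does not cure the text, because the article does not leave the time point open. It fixes one that fails for one of the two arrest types.

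**Stronger readings that the documents do not support.**

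- A reader might infer that the temperature exclusion is equally pre-arrest for in-hospital patients. It names no particular admission, and for a ward arrest ICU admission follows ROSC.
- A reader might assume an in-hospital share and count patients without a valid cardiac screen. The documents give no share, and such a count would also presume that no echocardiogram is done after ROSC.
- A reader might conclude that speed of implementation is not validly measured. The ROSC-to-start endpoint covers every patient, and medians and quartiles are reported alongside the mean, so one extreme value would be visible and would move the median little.

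**Conclusion.** The point holds for echocardiography. As worded, the only cardiac-function exclusions do not assess the heart after ROSC in a patient who arrests in the trial hospital. This rests on a literal reading of the criterion, and its effect in practice depends on how sites read it. It applies to one of the two arrest types enrolled, but its size in patients cannot be given. No effect on the sample size or the analysis method is shown; the stake is the safety screen and the consistency of eligibility between centres.

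The temperature criterion and the ICU-admission endpoint need clarification only. The first is ambiguous, and the second is affected solely by arrests in patients already in the ICU.

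**What to change.** - **Echocardiography:** reconcile the time point in Table 3 with the enrolled population, so that for in-hospital arrests the deciding echocardiogram is one obtained after ROSC and before inclusion. The thresholds stay with the sponsor.
- **Temperature:** state which admission is meant and how the criterion applies to a patient already in the ICU. Moving it to inclusion is not a neutral rewording: etiological treatment can fall between ICU admission and inclusion, so eligibility of out-of-hospital patients could change as well.
- **ICU-admission-to-start endpoint:** define it for patients already in the ICU at the time of arrest, or report those patients separately. Starting their clock at ROSC would only duplicate the neighbouring endpoint.

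The cost is a few words in Table 3 and one endpoint definition. The practical downside is a bedside echocardiogram after ROSC for in-hospital patients, within the time allowed for starting the procedure; out-of-hospital patients already need one on arrival.
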